### **Informed consent process**

Participation in the Study is voluntary. Several options to ensure potential participants have sufficient information and adequate understanding of the proposed research and the implications for participation will be made available, as follows:

- Participant information sheet
- Presentations on the study by the research team that may be attended by one or more staff from the same service
- Individual phone conversation about what it would mean to participate in the study in the way of purpose, method, demands, risks and potential benefits

With each of these options, potential participants will be invited to have a conversation with a member individually about what participation requires and an opportunity to ask questions.

It will be made clear in all options that not participating will not affect their relationship with their employer or the study team or involvement in future research. A reason for not participating is not required.

It will also be made clear that:

- That the service they are employed by is supportive of the study and has agreed to participation during paid working hours, access to a computer and the internet, on-site support being provided at the service.
- Participants will not be reimbursed for their time spent undertaking the training program
- Data collection is required to evaluate the Diabetes Training Program. We will cover what data will be collected, when including how often, the length of time data collection will take and the format for data collection (e.g., REDCap Survey).
- At any time participants may withdraw from the study without any penalty. The data they have provided can be withdrawn if they wish or can continue to be used in the study with their consent.

Potential participants themselves will have the ability to provide informed consent, no other person or statutory body is required to decide on their participation in the study.

As the methods of the study are pre-defined, full disclosure of the study protocol will be given.

**Training program:** A member of the research team will meet with each potential participant (either in person or via phone or video call) to explain the details of the study, review the Participant Information Sheet (Attachment 4), and provide the AHW/P or multidisciplinary health care providers an opportunity to ask the researcher any questions. If potential

participants participate in a team discussion about the project, they will have the opportunity to ask questions and may decide they do not want an additional one on one discussion.

Potential participants will be asked to take their time to think about participating and asked permission to be followed-up in 4-5 days. The research team follow up participants for a maximum of three times, either via email or phone conversation, over three weeks.

If the potential participant does agree to participate in the study, they will be asked to sign a Consent Form (Attachment 5) and email a copy back to a research team member.

In the event a participant signs the consent form without having discussed the project they will be followed up by the research team to ensure they clearly understand the program and participation. They will be given time to consider their participation, as outlined above.

**Interviews enablers and barriers:** Once potential participants flag interest in being interviewed, a research team member will discuss the purpose of the interviews, cover the details in the information sheet (Attachment 6) and what consenting means (Attachment 7). Potential participants will be given time to decide and be followed up 5 days after initial discussion for a maximum of three times over 3 weeks (Attachment 2).

**Systems assessment:** Only those interested in participating will turn up to hear about the study and the purpose of the systems assessment. Prior to starting the focus group, a research team member will go through the participant information sheet (Attachment 8) and consent form (Attachment 9) allowing time for questions. If potential participants would like to participate, they will be asked to sign the consent form.

**Medical record review:** A waiver of consent is being requested to receive medical record data collected in routine clinical practice. These data will provide insight into the effectiveness of the training program on patient outcomes. It is not feasible to ask permission of everyone across multiple services. A similar approach has been used by the research group to develop the SA Aboriginal Diabetes Strategy.

### **People in dependent or unequal relationships (National Statement Chapter 3.4)**

We recognise that employees (AHW/Ps & multidisciplinary health care providers) are in an unequal relationship with their manager.

The site managers will only provide the initial email informing staff of the study and then the research team will recruit participants. During recruitment and on the information sheet voluntary participation, it is clearly stated that non-participation will not jeopardise their employment or opportunities to be involved in further research. This will help mitigate coercion to participate.

To mitigate the potential for managers to prevent their staff from participating in the training program, the research team will first approach the service about the study and seek their support for their staff to participate; if they choose to participate a Collaborative Agreement (Attachment 10) will be entered into. During the development of the Collaborative Agreement service management will be required to approve staff time to participate and use computers, the internet and zoom facilities; this is to ensure that staff have the necessary resources to be able to participate.

## Sample

**Training program:** We will aim to recruit two participants per service. In discussions about the project with services, most services have more eligible staff. There must be at minimum one participant but is no upper limit to the number of participants from each service. The sample size will include an estimated uptake of (n=40) and accounted for drop-out rate of 50% of the AHW/P. Therefore, (n=20) participants would need to complete the training program.

**Interviews enablers and barriers:** We will aim to recruit between 3 and 15 participants of the training program given time and feasibility.

**Systems assessment:** The number of chronic disease staff who participate in the system assessment focus group will vary by service, depending on how large the team is and the number who consent to participate. There is no upper or lower limit to the number of staff who participate in the focus group; it depends on the staff willing to participate and who are available on the day.

**Medical record review:** Participants will not be recruited; Medical records (existing data) of people with diabetes in each participating service who meet the inclusion criteria will be audited retrospectively. The number of people with diabetes who receive care at each service enrolled in the study and meet the study inclusion criteria will vary. Prevalence of self-reported diabetes varies between 8 and 23% according to the 2018-19 ABS National Health Survey. It is therefore expected that between 8 and 23% of clients at each enrolled service will meet the eligibility criteria.

## Time period for recruitment

**Training program:** Three months is allocated to recruit participants.

**Interviews barriers and enablers:** Four weeks allocated to recruit participants inclusive of the last two weeks of the training program.

**Systems assessment:** Services will confirm their participation in the system assessment during the development of the Collaborative Agreement. This will be revisited during the first 12 months of the project at the time we are arranging to do the system assessment. Services can decide then or at any point that they do not want to be involved in the system assessment.

**Medical record review:** Services will confirm their participation in the medical record review during the development of the Collaborative Agreement. This will be revisited during the first 12 months of the project at the time we are arranging to collect data. Services can decide then or at any point that they do not want to be involved in the medical record review.

## b. Study procedures (Figure 3)

[figure not shown]

HS = Health Service  
 AHW/Ps = Aboriginal Health Workers & Practitioners  
 MDPs = Multidisciplinary health care providers  
 PSN = Peer Support Network (AHW/Ps only)  
 OS = Onsite Support

Figure 3: Study procedures flow diagram

## Enrolment of study sites

All primary health care services are aware of the study because they were all invited to participate in the co-design of the training program. The Aboriginal Health Council of South Australia advised that ethics approval was not required for the co-design of the training program. Many study sites have identified their interest in participating in the project. A Collaborative Agreement template has been developed (Attachment 10). The Collaborative Agreement outlines the roles, responsibilities and resource requirements of the research team and the health service, including study timeframes and data collection requirements. Site roles include allowing staff to participate in the project activities during work hours, staff access to internet, computer and zoom facilities, having a staff member who is not a study participant on the study Steering Committee.

## Randomisation

Randomisation will occur at the service level. Enrolled health services will be randomised into Group A and Group B. Randomisation and allocation will be undertaken after six months of providing PSN for all enrolled health service sites and prior to commencement of the training program. All enrolled health service sites will be listed, and a statistician will be responsible for randomizing the health service sites into cluster one (Group A participants) or cluster two (Group B participants) using a block size through a computer program for randomisation.

For the intervention assignment; a cluster crossover randomised trial will be employed in this study, as all participants receive the same intervention based on random service site allocation. Participants in the study sites will know which group they have been allocated after completing six months of the PSN, and before commencing the E-Learning module for group A. The project research team will not be blinded to group A or B allocation, only people analyzing the results will be masked/blinded.

**Peer Support Network (months 1-17):** Only AHW/Ps will participate in the PSN. AHW/P participants from both Group A and Group B will participate in the PSN for the entire duration of the study. The PSN will commence and convene for 6 months prior to Group A doing the e-learning modules and the OS. The PSN will run online via Teams, once a month, for 1.5 to 2 hours duration, and will be facilitated by a credentialed diabetes educator (DNE) who is a research team member.

As this is a pragmatic trial, it is understood that AHW/Ps may not be able to attend all PSN sessions due to competing work and/or personal priorities.

The PSN meetings will not be recorded. The PSN Facilitator will record participation in the network.

**E-Learning Modules (10 weeks):** There are 9 self-paced e-Learning modules. Each module takes approximately 1 hour to complete. Ten weeks have been allocated to complete the e-learning modules. All participants will do the e-learning modules. Services will have agreed to allow their staff to use the work computers and internet and to do the modules during work hours. These can also be done from any computer, at any time. The modules can be left and picked up at the same place for convenience during working hours.

**Onsite Support (minimum of twice over 10-week period):** The OS sessions will occur during the same 10-week period as the e-Learning modules. The OS will be face to face at the primary health care service. The number of OS sessions and what is covered during them will be negotiated between the participants and the OS Facilitator. It is suggested that each service hold a minimum of 2 sessions with the OS Facilitator. OS sessions will be held as a group, if there is more than one AHW/P or multidisciplinary health care providers within the health service. The group sessions will be held with AHW/Ps for the first half of the session and then include multidisciplinary health care providers for the remainder of the session. This format will be assessed and adapted as needed. This format responds to direct feedback during the co-design of the training program.

The OS will be facilitated by a credentialed diabetes educator (CDE) employed by Diabetes SA. The CDE will be a member of the research team.

**Group A:** At the start of month 7, AHW/P and multidisciplinary health care provider participants within the health services randomised to Group A will commence the e-Learning modules and OS, for a duration of 10 weeks. During this time, AHW/Ps from both Group A and Group B will continue to participate in the PSN.

**Wash out period (6 months):** There is a six month 'wash out' period where only the PSN is running. This will occur between Group A and Group B doing the e-Learning modules and participating in the OS.

**Group B:** After the 6-month washout period the participating AHW/Ps and multidisciplinary health care providers within the health services randomised to Group B will commence the e-Learning modules and OS, for a duration of 10 weeks. During this time, AHW/Ps from both Group A and Group B will continue to participate in the PSN.

### **Enabling and supporting on-going connection among the cohort**

A Microsoft Teams site will be created by the research team, who will manage the site so that only the research team can invite and remove members. All participants will be invited to the site. It will house diabetes-related resources approved by the study investigators or the Facilitators of the PSN and OS. One folder within the Teams site will be private only for PSN members. This folder will house the PSN materials. The research team and members will be able to post chats on the site to keep in contact. The chats will not be used as data in the study. The site will be administered and monitored by the research team predominantly the PSN Facilitator, OS Facilitator and Study Manager. On completion of the study, participants will be invited to keep the resources and the Teams site will be deleted by the research team.

During the training intervention a weekly email will go out to participants doing the training program to remind and keep participants moving through the modules (Attachment 11).

### **On-going communication**

A Friday update in the form of an email will be sent to participants (Attachment 12). This will include the status of the study in the form of a traffic light system and a highlight for the week which will be sourced from a reputable source such as Diabetes Australia, NDSS, RACGP. Each week we will introduce a research team member or a member of the diabetes health profession community including the Investigator team.

An e-newsletter will be produced every 2-months introducing the study, the study investigators, the research team, updates on project progress, links to diabetes resources, diabetes studies and showcasing diabetes organisations will be developed by the research team. It will be distributed to each site through the site representative on the study Steering Committee and to all participants, study investigators and key stakeholders. This will be an important form of communication during the intervention and post intervention. The Principal Researcher, [name] will be responsible for signing off on the Friday update and the e-newsletter.

## Time commitment of participants

Table 2 shows the time commitment by discipline, service, training component and data collection.

*Table 2: Time commitment*

|                                        | Peer Support Network        | Modules                                    | Onsite Support                  | Survey evaluations a                          | Interviews b      | System Assessment | Medical record review |
|----------------------------------------|-----------------------------|--------------------------------------------|---------------------------------|----------------------------------------------------------|------------------------------|-------------------|-----------------------|
| AHW/P c                     | 2 hours/month for 17 months | Maximum 1 hour for each module – 9 modules | Approx. 2-6 hours over 10 weeks | 10 minutes x 7 times
7 minutes x up to 17 times (PSN) | 1 hour once during the study |                   |                       |
| Multidisciplinary health care provider | n/a                         | Maximum 1 hour for each module – 9 modules | Approx. 2-6 hours over 10 weeks | 10 minutes x 7 times                                     | 1 hour once during the study |                   |                       |
| Service                                |                             |                                            |                                 |                                                          |                              | 2-3 hours         | 1 hour each time      |

a Demographics collected three times, will add 5 minutes; collection of primary outcome measures (knowledge, attitude, confidence, practice, skill)

b Does not include all participants

c Aboriginal Health Worker/Practitioner

## Participant withdrawal from the study

If a participant chooses to withdraw from the study before the initiation of data analysis, their data will be separated and will not become part of the study findings. If they chose to withdraw from the study after the data analysis, it will not be possible to retract their data. Any participant wishing to withdraw from the study can contact the research team via the telephone and/or email address provided in the Participant Information Sheet. Friday update and the e-newsletter will also have contact details of the research team and ethics committee approvals. Participants will be asked to complete a participant withdrawal form (Attachment 13).

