#### **Primary outcomes**

Directed Acyclic Graphs (DAGs) are being used to determine variables that need to be collected to adjust for potential confounding within statistical models. DAGs enable the conceptualisation of causal pathways. A DAG has been done for each primary outcome.

Generalized linear mixed effects models (GLMMs) with compound symmetric (exchangeable) correlation structure will be used to account for within health care centre (cluster) correlation; logit or log link will be used for binary outcomes such as prevalence resulting in mixed effect logistic regression, while log link will be used for count outcomes resulting in mixed effects negative binomial regression. GLMMs are a missing data method only assuming missing at random – MAR (instead of the more stringent MCAR – missing

completely at random). Effect measures will also be presented through calculation of number needed to treat and its associated 95% confidence interval. Analysis after the 12-month intervention follow-up is planned, spending  $\alpha=0.005$ .

In addition, a descriptive pre-post analysis of survey results due to participating in the PSN alone in the first six months will be calculated using appropriate parametric or non-parametric tests. These analyses will occur after each collection timepoint.

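### The withdrawal rule automatically discards data that the consent section lets participants leave in the study, and its cut-off has no fixed date

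*Protocol*

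**What the plan says.** Protocol section 10.b, Participant withdrawal from the study, sets two rules. For a participant who withdraws "before the initiation of data analysis, their data will be separated and will not become part of the study findings", exclusion is automatic and no choice is mentioned. For a later withdrawal: "If they chose to withdraw from the study after the data analysis, it will not be possible to retract their data".

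Section 10.a, Informed consent process, describes what participants are told: "At any time participants may withdraw from the study without any penalty". On the fate of the data it continues: "The data they have provided can be withdrawn if they wish or can continue to be used in the study with their consent". No cut-off is attached to either statement.

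Two other places bear on the consequences. Section 10.a, Sample, plans the numbers: "The sample size will include an estimated uptake of (n=40) and accounted for drop-out rate of 50% of the AHW/P", and "Therefore, (n=20) participants would need to complete the training program". Section 11.a, Primary outcomes, justifies the primary model by how it handles incomplete data: "GLMMs are a missing data method only assuming missing at random – MAR". The same section schedules descriptive pre-post analyses after every survey wave and a further analysis after the 12-month follow-up.

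**The concern.** A participant who withdraws before analysis and is content for earlier answers to be used must be kept under the consent section and excluded under the withdrawal section. A participant who withdraws after analysis and wants the data removed may have that under the consent section but not under the withdrawal section. The second conflict affects what people are promised at consent, as well as the analysis.

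Three statistical consequences follow if the withdrawal section is applied literally.

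- **Observed scores are lost.** A model that is valid under missing at random gets that validity from conditioning on what was observed. If someone leaves because of a score already recorded, keeping the score leaves the loss explained by observed data. Deleting it makes the loss depend on something the model can no longer see.
- **Deletion can be related to the arm.** Groups are told their allocation before Group A starts the modules. Between then and the 8.5-month survey (T2), Group A has nine modules and onsite support, which Group B does not yet have.
- **The trigger is open to interpretation.** The start of analysis could mean the first descriptive analysis at about month 6 or the analysis after the last survey at month 29. The project team is not blinded to allocation.

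**Working it through.** **1. The rules side by side**

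| Situation | Informed consent process | Participant withdrawal |
|---|---|---|
| Withdraws before analysis, agrees to continued use | Data kept | Data excluded |
| Withdraws before analysis, wants removal | Data removed | Data excluded |
| Withdraws after analysis, wants removal | Data removed (no cut-off given) | Removal not possible |
| Withdraws while analysis is under way | Participant's choice | Not covered |

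The rules agree only in the second row.

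**2. The plan's own figure.** Required completers 20, drop-out 50%: 20 / (1 − 0.5) = 40. This reproduces the stated uptake of 40. The 50% is given for Aboriginal Health Workers and Practitioners and refers to completing the training. It is not a rate of formal withdrawal, so it serves only as a loose upper bound on deletion.

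**3. How many people could be deleted.** Let f be the share of the 20 expected drop-outs who formally withdraw before analysis. The protocol does not give f, so it is varied. Number deleted = 40 × 0.5 × f. The last column is the standard-error ratio against keeping every score, sqrt(40 / remaining). It assumes equal loss in both groups, that the deleted people had given the score in question, and no clustering.

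| f | Deleted | Remaining | SE ratio |
|---|---|---|---|
| 10% | 2 | 38 | 1.03 |
| 25% | 5 | 35 | 1.07 |
| 50% | 10 | 30 | 1.15 |
| 100% | 20 | 20 | 1.41 |

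**4. Possible bias, on assumed inputs.** The protocol states no effect size, SD or correlation. A large-sample simulation therefore assumed a true effect of 0.5 SD, a correlation of 0.6 between baseline and outcome, a baseline-adjusted comparison, and withdrawal after the outcome was recorded. The same share was deleted in each arm. Where withdrawal was score-related, its log-odds fell by 1 per SD of outcome.

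| f | Share deleted | Random | Score-related equally in both arms | Score-related in trained arm only |
|---|---|---|---|---|
| 10% | 5% | 0.50 | 0.50 | 0.53 |
| 25% | 12.5% | 0.50 | 0.50 | 0.57 |
| 50% | 25% | 0.50 | 0.50 | 0.64 |
| 100% | 50% | 0.50 | 0.50 | 0.77 |

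Keeping all the data gives 0.50. Bias appears only in the last column and runs from 0.53 − 0.50 = 0.03 SD to 0.77 − 0.50 = 0.27 SD.

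**5. Who this applies to.** Randomisation follows six months of the Peer Support Network, so withdrawals in months 1 to 6 cannot depend on allocation. Someone who leaves during the ten training weeks, before T2, has no T2 score under either rule, and the added loss is the T0 and any T1 data. The bias in step 4 therefore concerns people who complete T2, then formally withdraw, and do so before analysis starts.

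**The case against.** The strongest reply is that this is a wording mismatch with a natural reconciliation. Exclusion would be the default and the consent section's choice would be exercised through the withdrawal form. That form (Attachment 13) is not among the documents at hand and may already record the choice. This stands as a caution about the form, but the withdrawal section as written still states exclusion without qualification.

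A reader might infer that half the participants will be deleted and the trial biased as a result. The documents do not support that. The protocol accepts missed sessions in a pragmatic trial, and people who do not finish the training are still participants who can be surveyed. Only those who choose to leave the study fall under the rule.

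A reader might also combine a bias of 0.25 SD with a 1.41-fold standard error. The first comes from w × g = 0.5 × 0.5: half of Group A deleted, scoring an assumed 0.5 SD lower, with no loss in Group B. The second needs half of both groups deleted. They are different scenarios. With 20 per group assumed and loss in Group A only, the ratio is sqrt((1/10 + 1/20) / (1/20 + 1/20)) = sqrt(0.15 / 0.10) = 1.22.

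Finally, it is tempting to keep all data unless removal is requested. That is not what the consent section offers: continued use depends on the participant's agreement. Section 13 also leaves ownership and control of the data with services and providers.

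**Conclusion.** The contradiction is established from the text alone: the two sections differ on whether a withdrawer's data may be kept and on whether they can be removed after analysis begins. The start of analysis is not a single date. Applied literally, the withdrawal section discards usable scores and weakens the missing-at-random basis of the primary model.

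The loss is 2 to 20 of 40 participants if 10% to 100% of the expected drop-outs formally withdraw, with the upper end unlikely to be reached. Bias is a risk and not a certainty. It is about zero when withdrawal is random or equally score-related in both arms. It reaches 0.03 to 0.27 SD only in the assumed case of score-related withdrawal in the trained arm alone. The protocol does not allow the true size to be derived. With about 40 participants, even a few deletions are worth preventing, and an analysis plan cannot recover data already removed under the protocol.

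**What to change.** Reword the withdrawal section to agree with the consent section:

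- On withdrawal, ask the participant whether data already provided may continue to be used.
- Where consent is given, keep the data and analyse them in the randomised group. Where the participant wishes removal, remove them.
- Define one calendar cut-off after which removal is no longer possible, and state it in both sections and at consent.
- Check that the withdrawal form separates stopping training, stopping surveys and removing data, and add these choices if it does not.
- Report the number of removals by group and by whether they came before or after randomisation.

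The cost is wording in the protocol and, if needed, the form, plus an ethics notification. Participants keep their right to have data removed up to the stated cut-off. The change is best made before withdrawals accumulate, since deleted data may not be recoverable.
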